#### Compliance, treatment satisfaction, and credibility

Treatment compliance and session evaluation will be assessed by the Treatment Satisfaction Scale (TSS) and Treatment Component Adherence Scale (TCAS), both of which have been used in previous trials [65]. The daily sleep diary will be used to examine the adherence to bright light therapy, where participants will be asked to record how long and at what times they used Re-Timers each day. The six-item Credibility-Expectancy Questionnaire (CEQ) will be used to assess treatment expectancy and credibility of the intervention [66].

### Statistical analysis

#### Sample size estimation

The target sample size was estimated based on the primary hypothesis using a priori power analysis. We expected a medium effect size (Hedges’ *g* = 0.30–0.47) based on the previous research [33]. Using *g* = 0.30 as a more conservative effect size, a total of 111 participants was estimated assuming a significance of 0.05 and an 80% power. Accounting for a 30% anticipated attrition rate, the final target sample size for the overall trial was 144 (*n* = 48 per arm).

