The Transdiagnostic Sleep and Circadian Intervention (TranS-C) is a programme that combined conventional therapeutic components from CBT-I with additional circadian-related components to address both sleep and circadian disturbances [27]. A series of studies have provided support for the TranS-C programme as a promising intervention for improving sleep and advancing the circadian phase in youths [28–30]. Specifically, in a study comparing the efficacy of TranS-C versus psychoeducation in 176 youths aged 10 to 18, TranS-C was found to result in significantly greater improvements in self-reported sleep and circadian measures at post-intervention [28]. In addition to the cognitive-behavioural approach, the use of chronobiotics has gained increasing attention as a therapeutic approach in recent years. Light is the most potent zeitgeber that entrains the endogenous circadian clock to the surrounding environment. Under controlled laboratory conditions, light has been shown to be effective in shifting the human circadian rhythm and subsequently used as a therapeutic intervention [31, 32]. In adults, bright light therapy (BLT) has been shown to improve circadian outcomes, insomnia symptoms, and depressive symptoms [33, 34]. However, the evidence of BLT in the youth population remains relatively limited. A study conducted by Gradisar et al. (2011) in adolescents with delayed sleep phase disorder, a clinical sleep disorder reflecting the extreme end of eveningness, showed moderate to large effects of CBT-I with adjunctive BLT in reducing sleep onset latency (*d* = 0.65–1.13), advancing bedtime and rise time (*d* = 0.89–1.24), and improving daytime functioning (*d* = 0.75–0.79) [35]. Nonetheless, previous research utilising light therapy in adolescents was mainly conducted in either mixed clinical samples [36] or those with delayed sleep phase disorder [35, 37]. It remains unclear how to address circadian issues in the context of youth insomnia, specifically whether CBT-I alone is sufficient to tackle eveningness in youths diagnosed with insomnia or if an adjunctive circadian-focused intervention, i.e. bright light therapy, could additionally address the circadian components of youth insomnia, thereby enhancing the treatment outcomes.

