### Study objectives

Given the gap in the current literature and the need to address circadian-related factors in youths with insomnia, this study aims to examine the efficacy of CBT-I and CBT-I plus bright light therapy in reducing insomnia severity in adolescents compared with a waitlist control. The secondary aim of the study is to examine the effects of CBT-I and CBT-I plus bright light therapy on mood symptoms and daytime functioning (e.g. sleepiness, fatigue, cognitive performance), as well as subjective and objective sleep and circadian measures.

The primary hypotheses for the trial are as follows:Both CBT-I and CBT-I plus BLT will lead to an improvement in self-reported insomnia symptoms by the end of treatment as compared to the waitlist control.CBT-I plus BLT will additionally lead to an advancement of chronotype and sleep onset by the end of treatment compared to the waitlist control.Changes in insomnia will mediate the changes in mood and other daytime symptoms.

The secondary hypotheses are as follows:CBT-I and CBT-I plus BLT will improve objectively measured sleep outcomes, mood symptoms, daytime functioning, and insomnia-related behaviours and cognitions by the end of treatment compared to the waitlist control.The treatment effects of CBT-I and CBT-I plus BLT will be maintained over time at 1 month and 6 months after treatment.

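### A total of 111 participants does not give 80% power for Hedges' g = 0.30; it fits a between-arm difference of about 0.64 to 0.73 SD

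*Protocol article*

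**What the plan says.** Under Sample size estimation, the protocol article expects a Hedges' g of "0.30–0.47) based on the previous research [33"] and takes the lower end, g = "0.30 as a more conservative effect size, a total of 111 participants was estimated assuming a significance of 0.05 and an 80% power". The total is then raised for 30% attrition to 144, or 48 per arm.

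The calculation is said to rest on the primary hypothesis. Under Study objectives, the first primary hypothesis is that each active arm "will lead to an improvement in self-reported insomnia symptoms by the end of treatment as compared to the waitlist control". Under Main analysis, the treatment by time interaction over three arms and two timepoints is taken as the treatment effect. Allocation is 1:1:1, so 111 is 37 per arm. The article does not name the test, its sidedness, the pre-post correlation or any conversion of g to another effect-size measure.

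**The concern.** Hedges' g is a difference between two group means in SD units. Detecting 0.30 SD at conventional error rates takes well over 100 per group, so 37 per arm looks far too few. Cohen's f, the spread of several group means in SD units, is a different scale, and f = 0.30 is a much larger effect than g = 0.30.

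The reader is told that the design has 80% power at a deliberately cautious effect. If it does not, a null result would be misread as evidence against a difference of 0.30 SD. That risk is greatest for the added light, because the effect size comes from a source that the introduction cites for light therapy in adults. The article also plans an interim look for efficacy and futility, and overstated power could mislead a judgement of futility.

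**Working it through.** **Inputs.** From Sample size estimation: g = 0.30 (range 0.30 to 0.47), significance 0.05, power 80%, N = 111, attrition 30%, 48 per arm. From Randomisation and masking: 1:1:1. Assumed, because the article does not state them: a two-sided test, SD = 1, and a pre-post correlation r varied from 0 to 0.8.

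**1. Where 111 comes from.** For a one-way analysis of variance the noncentrality is λ = f²N. With three groups, f = 0.30 and N = 111, λ = 0.09 × 111 = 9.99, and the noncentral F with 2 and 108 degrees of freedom gives power 0.803. At N = 110 it is 0.7996, so 111 is the smallest N that reaches 80%.

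A group by time interaction with two visits has λ = f²N × 2/(1 − r). With f = 0.15 and r = 0.5, λ = 0.0225 × 111 × 2/0.5 = 9.99. The two routes are algebraically identical.

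**2. What those routes mean as a difference d between arms.**
- Arm means (0, d, d): f = d√2/3, so d = 0.30 × 3/√2 = 0.64 SD.
- Arm means (0, d/2, d): f = d/√6, so d = 0.30 × √6 = 0.73 SD.
- For the two-visit interaction, the same differences in change give half these f values. So f = 0.15 again means 0.64 to 0.73 SD.

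**3. What g = 0.30 requires.** Per arm, n = 2(1.960 + 0.842)²/0.30² = 174.4, rounded up to 175. The noncentral t gives 176. A one-sided test would need 138. The three-arm overall test with means (0, 0.3, 0.3) has f = 0.141 and needs 486 in total.

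**4. Power at g = 0.30, unadjusted comparison at Week 7 (noncentral t).**

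| Analysed per arm | Power |
|---|---|
| 34 | 23% |
| 37 | 25% |
| 48 | 31% |

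The three-arm overall test at N = 111, means (0, 0.3, 0.3), has 24%. Even g = 0.47, the top of the stated range, has 51% power with 37 per arm.

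**5. Power for the planned test, 37 per arm.** A change score has SD √(2(1 − r)). A baseline-adjusted outcome has residual SD √(1 − r²). Dividing 0.30 by each gives:

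| r | Change (treatment by time) | Baseline-adjusted |
|---|---|---|
| 0 | 15% | 25% |
| 0.5 | 25% | 31% |
| 0.7 | 38% | 43% |
| 0.8 | 52% | 56% |

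Reaching 80% needs r of about 0.90 for change and 0.89 with baseline adjustment.

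**6. What the sample can detect with 80% power.** Unadjusted, or change at r = 0.5: 0.66 SD with 37 per arm. The article's own 48 per arm less 30% leaves 48 × 0.70 = 33.6, about 34, and then the figure is 0.69 SD.

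**The case against.** The best defence is that the planned test is the treatment by time interaction, not a bare Week 7 comparison, so it can gain from the pre-post correlation. This stands in part. A reader might infer that the trial's true power at g = 0.30 is simply 25%. The article does not support that, because 25% belongs to the unadjusted comparison or to the interaction at a correlation of 0.5. But the correlation needed to rescue 80% is about 0.89 to 0.90, too high to assume silently for a self-rated scale at assessments seven weeks apart. Pooling both active arms against waitlist (74 versus 37) gives only 31% in an unadjusted comparison.

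A reader might also infer that g was typed in as f. The match is exact, but the interaction route matches equally well and the article names no test, so this remains a guess. The test and correlation may be in the full protocol, and their absence here is not held against the plan.

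Nor does the error show that the comparison with waitlist is underpowered for the effect CBT-I really has. The article does not show which outcome or contrast supplied 0.30 to 0.47. The introduction cites the source for adults ("In adults, bright light therapy (BLT) has been shown to improve circadian outcomes, insomnia symptoms, and depressive symptoms"), which is not the contrast being powered, but whether CBT-I against waitlist gives more or less than 0.30 cannot be settled from the article. That is a question of justification, secondary to the arithmetic.

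Finally, data collection was due to end in December 2023, so enrolment is not at issue. This limits the remedy but does not make the statement correct.

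**Conclusion.** The sample size statement is wrong as written. Effect size, significance level, power and N are given together and are incompatible: g = 0.30 needs about 176 per arm, nearly five times the 37 provided (176/37 = 4.8). The total of 111 fits a difference of about 0.64 to 0.73 SD, more than twice the stated value. Power at g = 0.30 with 37 per arm runs from about 15% to 56% over correlations of 0 to 0.8 and the two forms of analysis.

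This rests on a two-sided 0.05 test, equal arms and g read in its usual sense. A one-sided test does not change the conclusion.

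**What to change.** Keep the enrolment and rewrite the sample size paragraph:
- Withdraw the claim of 80% power at g = 0.30.
- State that 48 randomised per arm with 30% attrition (about 34 analysed) gives 80% power for a difference of about 0.69 SD between an active arm and waitlist on the ISI at Week 7, unadjusted or as change at a correlation of 0.5. If 37 per arm are analysed, the figure is 0.66 SD.
- Name the test and state the pre-post correlation assumed. The detectable difference in change scales with √(2(1 − r)); at r = 0.7, for example, 0.69 × √0.6 = 0.53 SD.
- Give the basis for the target effect in terms of CBT-I against waitlist.
- State that the contrast of CBTI + BLT with placebo light is not powered at g = 0.30 and will be read from its confidence interval.

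The cost is one reworded paragraph and a less favourable stated detectable effect. No further participants are needed.

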### Randomisation and masking

Randomisation will be completed using simple randomisation with a 1:1:1 allocation ratio. A pre-randomised list with random sorting of the three trial arms will be generated in Microsoft Excel using the = RAND() function. As each participant enrols in the study, he/she will be sequentially assigned to the corresponding group in the pre-randomised list. The entire randomisation procedure will be completed by a trained research assistant who is not involved in other aspects of the trial. The project therapists and clinical assessors will be blinded to the group allocation. We do not anticipate any requirement for unblinding but if required, the Trial Manager, Data Coordinator, and Implementation Support Facilitators will have access to group allocations and any unblinding will be reported.

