#### Main analysis

The main analyses will be conducted following the intention-to-treat principle. Multilevel modelling (MLM) with restricted maximum likelihood estimation and an unstructured variance–covariance matrix will be used to analyse the main hypotheses on outcome measures. The use of MLM in analysing RCT data has the advantage of accounting for individual differences as a random effect [67–69]. MLM also has advantages over the traditional general linear model approach (e.g. mixed model repeated measures ANOVA) as it is unaffected by randomly missing data and can handle both time-dependent and independent covariates [67, 69]. Missing data for dependent variables will be assumed to be missing at random and accounted for by the maximum likelihood estimation. Two sets of MLMs will be conducted; one will include three treatment arms (CBTI + BLT vs CBTI-BLT vs WL) and two timepoints (pre-treatment vs post-treatment) as fixed effects; the second set will consist of two treatment arms (CBTI + BLT vs CBTI-BLT) and four timepoints (pre-treatment vs post-treatment vs 1-month follow-up vs 6-month follow-up) as fixed effects. The treatment × time interaction will also be included as a fixed effect on both MLMs and will be considered the treatment effect, while repeated measures will be nested within individual participants as random intercepts. A *p*-value of 0.05 represents statistical significance in all analyses. The *p*-values on outcome measures will be adjusted using the Benjamini–Hochberg procedure with a false discovery rate set as 20% to account for multiple comparisons.

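### The stated 80% power at Hedges' g = 0.30 with 111 participants does not hold for a between-arm difference; 37 per arm gives about 25% at a pre-post correlation of 0.5

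*Protocol article*

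**What the plan says.** Under Sample size estimation, the protocol article says: "The target sample size was estimated based on the primary hypothesis using a priori power analysis". It expects Hedges' g between 0.30 and 0.47 from a cited source, takes the lower end and, with that value "as a more conservative effect size, a total of 111 participants was estimated assuming a significance of 0.05 and an 80% power". It then allows for 30% attrition and arrives at 144, or 48 per arm. It names no test, sidedness, pre-post correlation or conversion from g to another effect-size scale.

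Under Study objectives, the first primary hypothesis is that both active treatments "will lead to an improvement in self-reported insomnia symptoms by the end of treatment as compared to the waitlist control". Under Randomisation and masking: "Randomisation will be completed using simple randomisation with a 1:1:1 allocation ratio".

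Under Main analysis, the first model set has "three treatment arms (CBTI + BLT vs CBTI-BLT vs WL) and two timepoints (pre-treatment vs post-treatment) as fixed effects", and "The treatment × time interaction will also be included as a fixed effect on both MLMs and will be considered the treatment effect".

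**The concern.** Hedges' g is a standardised difference between two means, and the first primary hypothesis compares each active arm with waitlist. Read that way, effect, significance level, power and sample size cannot all be true together. This is not a detail left to an analysis plan, because the article states all four in one sentence.

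At stake is what the trial can be said to detect. A reader told that power is 80% at the low end of the expected range would take a non-significant comparison with waitlist as fairly strong evidence against a difference of 0.30 SD. The design does not support that reading.

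**Working it through.** **Inputs from the protocol article.** g = 0.30 (upper end 0.47), significance 0.05, power 80%, N = 111, 30% attrition and final N = 144 (Sample size estimation); 1:1:1 allocation (Randomisation and masking), so 111/3 = 37 per arm; three arms by two timepoints (Main analysis).

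**Assumptions not in the documents.** Two-sided testing; pre-post correlation r, shown from 0.3 to 0.9; g in units of the SD at a single timepoint.

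**1. Reproducing 111.** Noncentral F, 2 and N − 3 degrees of freedom, N in multiples of 3. Two routes give it:

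- One-way ANOVA, three groups, f = 0.30: λ = f²N = 0.09 × 111 = 9.99, power 0.803 (0.792 at N = 108).
- Treatment-by-time interaction, three groups, m = 2 timepoints, f = g/2 = 0.15, r = 0.5: λ = f²Nm/(1 − r) = 0.0225 × 111 × 2/0.5 = 9.99, again 0.803. With r = 0.3 this route gives 153, and with r = 0.7 it gives 69.

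The two are numerically identical, so the figure 111 cannot show which was used.

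**2. What those f values mean between arms.** Suppose both active arms differ from waitlist by 0.30 SD. The SD of the arm means (0.30, 0.30, 0) is 0.30 × √(2/9) = 0.141. So f is 0.14 in the one-way ANOVA and, with the change split over two timepoints, 0.071 in the interaction. Conversely, f = 0.30 corresponds to 0.30/0.471 = 0.64 SD if the active arms are equal, or 0.30/0.408 = 0.73 SD if the arms are evenly graded. At r = 0.5 the interaction route implies the same differences in change.

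**3. Sample size for g = 0.30.** Two-sample noncentral t, 80% power: 176 per arm (175 by the normal approximation).

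**4. Pairwise power.** Noncentrality d√(n/2), with d = g/√(2(1 − r)) on change and d = g/√(1 − r²) with baseline adjustment. For example, n = 37, r = 0.5, on change: d = 0.30, noncentrality 0.30 × √18.5 = 1.29, power 24.7%. At g = 0.30:

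| r | 37/arm, change | 37/arm, adjusted | 33–34/arm, change | 33–34/arm, adjusted |
|---|---|---|---|---|
| 0.3 | 19% | 27% | 17–18% | 24–25% |
| 0.5 | 25% | 31% | 22–23% | 28–29% |
| 0.7 | 38% | 43% | 34–35% | 39–40% |
| 0.8 | 52% | 56% | 47–49% | 52–53% |
| 0.9 | 81% | 83% | 77–78% | 79–80% |

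The three-arm interaction test with means (0.30, 0.30, 0) and r = 0.5 has λ = 0.005 × 111 × 2/0.5 = 2.22 and power 24%.

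**5. Completers under the plan's own attrition.** 144 × 0.70 = 100.8, or 33.6 per arm. The 144 is 111 × 1.3 = 144.3; retaining 111 would take 111/0.70 = 159. This is why the table has columns for 33 to 34 per arm.

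**6. Detectable difference.** With 37 per arm and r = 0.5, 80% power needs about g = 0.66 on change (0.57 adjusted). With 33 to 34 per arm it needs 0.69 to 0.70 (0.60 to 0.61 adjusted). At g = 0.47 with 33 to 34 per arm and r = 0.5, power is 47–48% (58–60% adjusted).

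**The case against.** **The planned test is the interaction, and 111 follows from it.** It does, with f = 0.15 and r = 0.5, and this route matches the Main analysis. But halving g to get f is the rule for a two-group comparison at one time. In the planned interaction, f = 0.15 stands for roughly twice the stated difference.

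**Repeated measures add power.** True, and it means 25% should not be quoted without its r. But nothing from r = 0.3 to 0.8 comes near 80% at g = 0.30.

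**The hypotheses are directional.** One-sided testing with 37 per arm and r = 0.5 gives 36%. That is still far short.

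**The true effect on the Insomnia Severity Index may be larger.** This stands. The documents do not show that 0.30 is the likely difference from waitlist; it comes from a source not available here. At g = 0.47 with 33 to 34 per arm, power passes 80% if r is about 0.8. So the trial is not shown to be too small for its primary comparison. What is wrong is the power stated at 0.30.

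**Stronger readings that the documents do not support.** A reader might infer that g was mistakenly entered as a three-group f. Since a second route gives the same 111 and the article names neither, that is conjecture. A reader might also infer that the trial falsely promises 80% power for CBT-I with active versus placebo light. The sample size is tied to the primary hypothesis, whose comparisons are with waitlist, so no power is promised for that contrast.

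**Conclusion.** The statement of 80% power at Hedges' g = 0.30 with 111 participants is wrong for a between-arm standardised difference. With 37 per arm, power on change is 19% to 52% for r from 0.3 to 0.8 (27% to 56% baseline-adjusted), and 25% (31%) at r = 0.5. A correlation of about 0.89 to 0.90 would be needed for 80%. Under the plan's own attrition the figures are a few points lower.

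The sizes rest on two-sided testing, on g in single-timepoint SD units and on an assumed r. If g were instead in units of the SD of change, 37 per arm would give 25% whatever r is. How 111 was obtained remains unknown.

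**What to change.** Without changing enrolment, replace the power statement under Sample size estimation with wording such as:

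*With about 33–34 completers per arm the trial has 80% power for a between-arm difference in ISI change versus waitlist of about g = 0.69–0.70 (0.60–0.61 baseline-adjusted), assuming r = 0.5; power at g = 0.30 is about 22–23% (28–29% adjusted) and at g = 0.47 about 47–48% (58–60% adjusted).*

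Give the range over r beside it, and name the test, its sidedness and the correlation assumed. Remove the claim of 80% power at g = 0.30 and the description of that value as the more conservative choice.

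The cost is wording only: no added participants and no change to the hypotheses or the model. The downside is that a published figure becomes less favourable. The article expected data collection to finish by the end of December 2023, so correcting the statement is the proportionate remedy.

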**Methods:**

We will carry out a randomised controlled trial (RCT) with 150 youths aged 12–24 who meet the criteria of insomnia and eveningness. Participants will be randomised into one of three groups: CBT-I with bright light therapy, CBT-I with placebo light, and waitlist control. Six sessions of CBT-I will be delivered in a group format, while participants will be currently asked to use a portable light device for 30 min daily immediately after awakening throughout the intervention period for bright light therapy. The CBT-I with light therapy group will receive bright constant green light (506 lx) while the CBT-I with placebo light group will receive the modified light device with the LEDs emitting less than 10 lx. All participants will be assessed at baseline and post-treatment, while the two active treatment groups will be additionally followed up at 1 month and 6 months post-intervention. The primary outcome will be insomnia severity, as measured by the Insomnia Severity Index. Secondary outcomes include self-reported mood, circadian, daytime functioning, and quality of life measures, as well as sleep parameters derived from actigraphy and sleep diary and neurocognitive assessments. Objective measures of the circadian phase using dim-light melatonin onset assessment and sleep parameters using polysomnography will also be included as the secondary outcomes.

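### The 30% attrition allowance is multiplied on (111 × 1.30 = 144) instead of divided out (111 / 0.70 = 159), and the abstract gives an unexplained 150; neither total keeps 111 participants at 30% loss

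*Protocol article*

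**What the plan says.** Three totals appear in the protocol article.

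- Sample size estimation gives the number the power calculation requires: "a total of 111 participants was estimated assuming a significance of 0.05 and an 80% power". The effect size is a Hedges' g of 0.30, taken "as a more conservative effect size".
- The same section then allows for loss: "Accounting for a 30% anticipated attrition rate, the final target sample size for the overall trial was 144", which it splits as 48 per arm.
- The abstract (Methods) says: "We will carry out a randomised controlled trial (RCT) with 150 youths aged 12–24".

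Allocation is equal across three arms: "Randomisation will be completed using simple randomisation with a 1:1:1 allocation ratio". So 111 corresponds to 37 per arm, 144 to 48 and 150 to 50. Nothing in the article explains the step from 144 to 150.

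**The concern.** An attrition rate is a share of the people enrolled. To finish with 111 after losing 30%, the enrolled number must satisfy N × 0.70 = 111. Adding 30% of 111 on top gives a smaller number, because the 30% is then taken of the wrong base. The article says attrition has been accounted for, but at the stated rate it has been only partly covered.

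The stated 80% power belongs to 111 participants. If fewer provide the outcome, the power claim no longer follows from the article's own inputs. The abstract's 150 differs from the target in the methods and does not close the gap either.

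**Working it through.** **Inputs from the article.** Required number 111 (37 per arm); significance level 0.05; power 80%; attrition 30%; targets 144 (Sample size estimation) and 150 (abstract); three equal arms.

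**Step 1: reproduce the stated 144.**
- Multiplying: 111 × (1 + 0.30) = 144.3. Per arm, 37 × 1.30 = 48.1, taken as 48, and 48 × 3 = 144. This matches.
- Dividing: 111 / (1 − 0.30) = 158.57, rounded up to 159. Per arm, 37 / 0.70 = 52.86, rounded up to 53, and 53 × 3 = 159. This matches neither 144 nor 150.

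Multiplication therefore reproduces the stated figure and division does not.

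**Step 2: what each total leaves at 30% loss.**

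| Enrolled | × 0.70 | Per arm | Against 111 |
|---|---|---|---|
| 144 | 100.8 | 33.6 | about 10 short |
| 150 | 105.0 | 35.0 | 6 short |
| 159 | 111.3 | 37.1 | met |

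**Step 3: the attrition each total supports.**
- 144: 1 − 111/144 = 0.229, i.e. 22.9%.
- 150: 1 − 111/150 = 0.260, i.e. 26.0%.

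Steps 1 to 3 use only figures printed in the article.

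**Step 4: size of the power loss (rests on assumptions).** The article does not name the test or all the inputs behind 111, so this step needs a reconstruction. Two noncentral F calculations give 111 as the smallest equal-arm total with at least 80% power:
- (a) One-way comparison of three groups with Cohen's f = 0.30: noncentrality λ = N × 0.30² = 0.09N, with 2 and N − 3 degrees of freedom.
- (b) Interaction of three groups by two timepoints with f = 0.15 (half of 0.30) and an assumed within-person correlation of 0.5: λ = N × 0.15² × 2 / (1 − 0.5) = 0.09N, with (3 − 1)(2 − 1) = 2 and N − 3 degrees of freedom.

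The noncentrality and degrees of freedom coincide, so both routes give the same power:

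| Participants with outcome data | λ | Power |
|---|---|---|
| 111 | 9.99 | 80.3% |
| 105 | 9.45 | 77.9% |
| 101 | 9.09 | 76.2% |

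Route (b) depends on the correlation. At 0.3, 0.4, 0.6 and 0.7 the required total becomes 153, 132, 90 and 69. Of the values tried, only 0.5 returns 111.

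**The case against.** **Timing of the loss.** The article does not say at which visit 30% attrition is expected. The first primary hypothesis concerns the end of treatment (Study objectives), while the active arms are followed for 6 months afterwards (Procedures). If 30% refers to the whole follow-up, loss at Week 7 could be smaller, and 144 would suffice up to 22.9%. This stands. A reader might infer that the trial will definitely miss 80% power, but the shortfall is conditional on 30% loss by the post-treatment assessment.

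**Partial data.** The planned multilevel model (Main analysis) keeps participants with incomplete data. With only two timepoints in the primary comparison, someone without a post-treatment score contributes no observed change, so the gain is slight. The sample size section claims no credit for partial data, and its decision to inflate implies that losses have to be replaced. This softens the loss and leaves the inflation wrong.

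**Effect-size metric.** A reader might infer from route (a) that the authors powered the trial on a Cohen's f of 0.30. The article states a Hedges' g and never an f, and route (b) reaches the same 111 from f = 0.15. The text cannot decide between them, so the power figures are a reconstruction and should not be attributed to the authors.

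**Which target governs.** A reader might also infer that no governing target can be identified. That goes too far: the sample size section says "the final target sample size for the overall trial was 144". The abstract's 150 is an unreconciled figure above that target, which is a real but minor inconsistency.

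**Consequence.** The loss is 2 to 4 percentage points of power, and Trial status expects data collection to end in December 2023. This limits the seriousness of the point without making the stated figure right.

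**Conclusion.** The point holds as an error of arithmetic and reporting. The article inflates 111 by a factor of 1.30 where a 30% attrition rate requires division by 0.70, so 144 stands where 159 would follow from its own inputs. The abstract's 150 is unexplained and also falls short of 159.

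The totals of 144 and 150 support 22.9% and 26.0% attrition. That result needs no assumption. The shortfall of about 10 or 6 participants assumes that 30% are lost by the post-treatment assessment. The fall in power from 80.3% to about 76% or 78% further assumes one of the two reconstructions of 111, and takes no credit for partial data.

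This should be corrected, but it changes no comparison, analysis or conclusion of the trial.

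**What to change.** State one target in both the abstract and the sample size section. Then do one of the following:

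- State the attrition that the target supports: 22.9% for 144, or 26.0% for 150.
- Keep 30%, say at which assessment it is expected, and report the resulting number with outcome data (about 101 or 105) together with the correspondingly lower power. The authors should compute that power from the inputs of their own calculation, since the 76% and 78% here come from a reconstruction.

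The cost is wording in two places and a slightly less favourable power statement. No additional enrolment is needed and the analysis does not change.
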